#### Secondary Outcome Measures

We shall also collect pragmatic efficacy, tolerability, and functional outcome measures in both cohorts. These will include evaluations during the follow-up period regarding hospital admissions; visits to accident and emergency departments and outpatient clinics; changes in and number of medications; changes in antipsychotic dose over time; use of chlorpromazine dose equivalents as reference; type and number of side effects, including impact on BMI; and initiation or return to work or academic activities.

As part of routine practice, patients in cohort 1 will also be assessed using the quality-of-life self-completion questionnaire EQ-5D-5L to determine overall improvement over time. Scores from this questionnaire will also feed into the 5SPM step 5 to make treatment decisions at month 6. This cohort will also be evaluated using a battery of questionnaires, including the Positive and Negative Syndrome Scale [21], Calgary Depression Scale for Schizophrenia [22], Brief Negative Symptom Scale [23], and Udvalg for Kliniske Undersøgelser Side Effect Rating Scale [24].

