### Participants

A total of 300 patients will be included in this project. We shall include 2 different cohorts. Cohort 1 will be a prospective sample of patients with first-episode psychosis referred over 18 months to the new early intervention in psychosis program of personalized precision psychiatry (PRINT) at CAUSA. Cohort 2 will be a retrospective, consecutive (in reverse chronological order as registered in the CAUSA electronic health records) sample of patients who experienced a first episode of psychosis before the implementation of PRINT.

Inclusion and exclusion criteria for both cohorts will be aligned with the PRINT program referral acceptance criteria, which are predominantly inclusive.

Inclusion criteria are as follows: patients (1) with a diagnosis of first-episode psychosis, either nonaffective or affective; (2) aged 12 to 35 years; and (3) followed by clinical services for at least 1 year or earlier if there was evidence of antipsychotic treatment discontinuation (see the Outcome Measures section). In addition, patients in cohort 1 or their family or legal representatives will have to provide written consent to take part in the CLUMP project, including pharmacogenetics analysis (see the Ethical Considerations section). For patients in retrospective cohort 2, this will not be an inclusion criterion, but all of them will be approached by our research team seeking their consent to obtain their pharmacogenetic profile for research purposes.

Exclusion criteria are as follows: patients (1) with first-episode psychosis due to organic causes, for example, brain diseases such as Huntington or Parkinson disease, HIV, syphilis, dementia, brain tumors or cysts, or brain injury; (2) with moderate to severe intellectual disability; and (3) who spent (cohort 2) or plan to reside during (cohort 1) most of the 1-year follow-up period in a locality out of the PRINT program’s catchment area.

For additional comparative purposes, we shall analyze the environmental, clinical, and pharmacogenetic information of patients with psychotic disorders of more than 5 years of evolution or with other mental disorders whose data are currently stored and have been ethically approved for research use in our unit of pharmacogenetics and precision medicine at the HUS.

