### Outcome Measures

#### Primary Outcome Measure

The primary outcome to measure treatment adherence will be all-cause discontinuation of the initially prescribed antipsychotic medication following the patient’s or treating clinician’s decision. All-cause discontinuation rates in the CLUMP project will be defined by all-cause discontinuation proportions during the 1-year follow-up and the mean time to such discontinuation.

For cohort 1, the 1-year follow-up period will start when an antipsychotic medication is prescribed taking into consideration the pharmacogenetics advice emerging from the 5SPM method. For cohort 2, follow-up would begin on the date when the first antipsychotic medication was prescribed. For both cohorts, the first prescribed antipsychotic will be the initially prescribed antipsychotic drug for maintenance treatment, not only for short-term use to control psychomotor agitation. In addition, in accordance with existing scientific consensus, the discontinuation date will be defined as the first day of a 2-week or longer interruption of the first prescribed antipsychotic. In cohort 2, treatment discontinuation dates will be determined by examining clinical records. Where only approximate dates are available, the first, middle, or final day of the month will be used as best estimates. In cases in which cross-titration of medication took place, the date of discontinuation will be the first day of the cross-tapering process.

All-cause discontinuation will also be stratified by 4 reasons: insufficient efficacy, adverse events, lack of adherence, and other. Insufficient efficacy will be established at the treating clinician’s judgment only after at least 3 weeks of treatment. If more than one reason for discontinuation was present, we shall select one by applying the ranking order as stated previously.

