### Statistical Analysis

Comparisons of the main outcome (ie, discontinuation rates) will be carried out using the chi-square test. Kaplan-Meier survival curves and multivariate log rank tests will be used to assess time to all-cause antipsychotic discontinuation. For these analyses, patients will be followed up on for a year, from antipsychotic treatment initiation until discontinuation. Thus, we shall censor survival time by the end of the 1-year observation period or before such date if there is enough evidence of antipsychotic discontinuation. We shall describe and compare sociodemographic information and clinical and functional outcomes within and between groups. Means and SDs will be used to describe quantitative variables. We shall use the chi-square test or Fisher exact test for categorical variables and Mann-Whitney *U* test for continuous variables, among others. Data analyses will be conducted using the R statistical software (version 4.4.2 for Windows).

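### Side effects are to be compared between cohorts, but only cohort 1 is assessed with a structured side-effect scale, so the counts may not be comparable

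*Protocol article*

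**What the plan says.** All places are in the Protocol article.

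- **Shared outcome.** Secondary Outcome Measures opens with "We shall also collect pragmatic efficacy, tolerability, and functional outcome measures in both cohorts". The list that follows includes "type and number of side effects, including impact on BMI".
- **Instrument in one cohort.** The next paragraph of that section turns to cohort 1: "This cohort will also be evaluated using a battery of questionnaires, including the Positive and Negative Syndrome Scale". The same sentence ends the battery with the "Udvalg for Kliniske Undersøgelser Side Effect Rating Scale". No such assessment is described for cohort 2.
- **How the cohorts arise.** Under Participants, "Cohort 1 will be a prospective sample of patients with first-episode psychosis", whereas "Cohort 2 will be a retrospective, consecutive (in reverse chronological order as registered in the CAUSA electronic health records) sample". Clinical Management and Pharmacogenetics Analysis adds that cohort 2 was treated by generic community teams.
- **Source of data in cohort 2.** Primary Outcome Measure states "In cohort 2, treatment discontinuation dates will be determined by examining clinical records". No section names the source of cohort 2 side effects.
- **Comparison.** Statistical Analysis states "We shall describe and compare sociodemographic information and clinical and functional outcomes within and between groups", using chi-square, Fisher exact and Mann-Whitney tests among others.
- **Limitations.** This section names the single centre and a possible status quo bias in cohort 1. It does not mention unequal ascertainment.

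**The concern.** A count of side effects depends on how hard one looks. A rating scale asks every patient about a fixed list of symptoms. A routine note holds what the patient mentioned and the clinician chose to write down. If cohort 1 is questioned systematically and cohort 2 is read from past notes, the two counts are not the same variable, even if both carry the same name in the dataset. Keeping the scale scores in a separate file does not fully solve this, because symptoms found with the scale can be written into the cohort 1 notes.

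Tolerability matters to the rationale. The Introduction names adverse reactions as a significant contributor to stopping treatment, and credits the 5SPM approach, in earlier work in poor responders, with lowering the risk of adverse effects. A comparison that counts more completely in the 5SPM cohort could hide a real improvement or show an apparent harm. Later analysis cannot repair this, since symptoms never asked about or recorded in cohort 2 cannot be recovered.

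**Working it through.** **Is there a figure in the plan to reproduce?** Not for this comparison. The only calculated figure, 38 per cohort in Effect and Sample Size, concerns discontinuation (0.4 against 0.1). It reproduces: h = 2·asin(√0.4) − 2·asin(√0.1) = 0.726; n = 2·((1.960 + 0.842)/0.726)² = 29.8, rounded up to 30; 30/0.8 = 37.5, rounded up to 38. It has no bearing on side effects.

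**Inputs.** From the article: 50 patients per cohort, expected loss 0.2, two-sided 5% level. Assumed, because the article gives none: true side-effect frequencies and the share of them captured in each cohort.

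**A. Mean number of side effects.** Observed ratio = true ratio × (capture in cohort 1 / capture in cohort 2). Assume true means of 1.5 in cohort 1 and 2 in cohort 2, a true ratio of 1.5/2 = 0.75. The observed ratio exceeds 1 when the capture ratio exceeds 2/1.5 = 1.33. With capture of 0.9 in cohort 1:

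| Capture in cohort 2 | Observed means (cohort 1, cohort 2) | Observed ratio |
|---|---|---|
| 0.9 | 1.35, 1.80 | 0.75 |
| 0.7 | 1.35, 1.40 | 0.96 |
| 0.5 | 1.35, 1.00 | 1.35 |
| 0.3 | 1.35, 0.60 | 2.25 |

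**B. If the scale reaches the compared count only in part.** Let c be routine capture in both cohorts, and f the share of the additional symptoms found by the scale (up to 0.9) that enters the cohort 1 notes. Capture in cohort 1 is then c + f(0.9 − c), and the sign reverses when this exceeds 1.33c.

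- c = 0.5: 0.5 + 0.4f > 0.667, so f > 0.42.
- c = 0.3: 0.3 + 0.6f > 0.4, so f > 0.17.
- c = 0.7: 0.933 would be needed, above the 0.9 available, so the sign does not reverse, though the benefit shrinks.

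**C. Proportion with a given side effect, no true difference.** Observed rate = true rate × detection. Detection in cohort 1 is 0.9, with 50 per cohort. Entries are the chance of a significant uncorrected chi-square result against cohort 1, by exact binomial enumeration.

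| True rate | Detection in cohort 2: 0.9 | 0.7 | 0.5 | 0.3 |
|---|---|---|---|---|
| 30% | 2.5% | 11% | 32% | 68% |
| 50% | 2.8% | 18% | 56% | 92% |
| 70% | 2.5% | 31% | 83% | 99% |

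With 50 × 0.8 = 40 per cohort and a true rate of 50%, the last three columns become 15%, 47% and 85%.

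**D. A true benefit.** Take true rates of 50% in cohort 1 and 70% in cohort 2, with 50 per cohort. The chance of a significant result in favour of cohort 1 is 46% with equal detection of 0.9. It falls to 7% if detection in cohort 2 is 0.7, and to 0.2% if it is 0.5. The observed rates are equal when cohort 2 detection is 0.45/0.70 = 0.64.

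**The case against.** The strongest reply is that the article never says the scale feeds the comparison. Its second paragraph on secondary outcomes reads most naturally as adding a battery to the measures shared by both cohorts, so a reader who infers that scale scores are the compared count goes beyond the text. This stands. What remains is that nothing keeps scale-elicited symptoms out of the cohort 1 count; spill-over into the notes is plausible but not described.

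A reader might also infer that the article states that cohort 2 side effects come only from past records. It does not. Records are named for discontinuation dates. Data Management lists interviews, record review and blood tests without assigning them to cohorts. The contact with cohort 2 patients described under Participants is to seek consent for pharmacogenetic profiling. Records are the likely source, not the stated one, and interviews held later would not match prospective questioning either. A condensed article may leave abstraction rules to the full protocol, so their absence alone is no error. The point rests on what is stated: the same outcome in both cohorts, a side-effect instrument in one, and a comparison between them.

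It is also fair to say that tolerability does not rest on the count alone. Discontinuation for adverse events, medication and dose changes, and BMI are already planned. These are not captured identically either: the month-6 step 5 review uses questionnaires to inform treatment, so treatment actions in cohort 1 depend partly on structured assessment, and the acknowledged status quo bias could suppress them. They depend less on elicitation, but they are not free of it.

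**Conclusion.** The concern holds in a limited form. As written, the plan compares side effects between a cohort assessed with a structured scale and a retrospective cohort for which no such assessment is described, and it does not acknowledge the difference. The count may be inflated in cohort 1 relative to cohort 2.

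The size is unknown. The illustrations show that plausible gaps in capture could reverse a 25% reduction (capture ratio above 1.33) or make a false finding against cohort 1 likely, but every capture rate and side-effect frequency in them is assumed.

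Two stronger conclusions are tempting and not supported. The first is that the comparison is biased on balance against the pharmacogenetic cohort. Unequal elicitation pushes that way, but service model, period and status quo bias may push either way, so the net direction is uncertain. The second is that the main result is compromised. This point concerns a secondary outcome; it does not touch the primary outcome or the sample size. BMI is measured rather than elicited, so its main difficulty is likely to be missing past values.

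**What to change.** - **Secondary Outcome Measures and Statistical Analysis:** state that the compared side-effect outcome is taken in both cohorts from routine clinical records, with one abstraction form and the same rules, excluding entries that come from the structured scale. Report scale results within cohort 1 only.
- **Weight of evidence:** rest the between-cohort tolerability comparison mainly on items already planned for both cohorts that depend less on elicitation, namely discontinuation for adverse events, medication and dose changes, and routinely recorded BMI. Treat any total count of side effects as descriptive.
- **Limitations:** add unequal ascertainment, and note that symptoms elicited by the scale and the structured month-6 review can still influence cohort 1 notes and treatment actions.

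The cost is wording and one abstraction form, with no new visits. Data collection is expected to run until June 2027, so the change is still feasible. The downside is that milder side effects carry less weight between cohorts, and some asymmetry remains.

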### Effect and Sample Size

We conducted a power calculation for the main outcome: the proportion of patients with first-episode psychosis who, by their treating clinician’s or their own decision, discontinue, for any reason, the first prescribed antipsychotic medication within 1 year. As stated previously, recent research studies, mostly carried out in early intervention settings, concur that 40% of patients with first-episode psychosis experience first prescribed antipsychotic drug discontinuation during the first year following treatment initiation [7,8]. This proportion may be even higher in patients receiving mainstream psychiatric care, such as our cohort 2. Considering the expectations behind the use of personalized precision medicine, PRINT should aim to reduce discontinuation rates to 10%. Therefore, for a power of 80% with (1) a significance level of .05 (2-sided), (2) all-cause discontinuation rate in cohort 1 (intervention) of 0.4, (3) all-cause discontinuation rate in cohort 2 (treatment as usual) of 0.1, and (4) an expected dropout or loss to follow-up rate of 0.2, our calculations would require a sample size of at least 38 patients in each cohort. We used the R statistical software *pwr* package for this calculation (version 4.4.2 for Windows; R Foundation for Statistical Computing).

In CAUSA, we have found an administrative incidence of 50 new patients aged 12 to 35 years every year. Thus, we would expect at least 75 patients eligible to be recruited for cohort 1 over 18 months. Using a conservative approach, if 25 patients (approximately 35%) do not agree to take part, we would still enroll 50 patients. This would be in addition to another 50 patients in our retrospective cohort 2 and pharmacogenetic data currently available at CAUSA from 100 patients with psychotic disorders of more than 5 years of evolution and another 100 patients with other mental disorders that we shall use for further comparative purposes, as outlined previously. This all accounts for a total of 300 participants contributing to this project.

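### The only test named for continuous outcomes cannot adjust for anything, although the cohorts are not randomised; for BMI, one regression would be a cheap, low-priority improvement

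*Protocol article*

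**What the plan says.** Secondary Outcome Measures lists, for both cohorts, "type and number of side effects, including impact on BMI". It gives no time point or scale for the BMI comparison.

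Statistical Analysis states: "We shall describe and compare sociodemographic information and clinical and functional outcomes within and between groups". For continuous variables it names the Mann-Whitney U test and leaves room for others. Its only multivariable wording concerns log rank tests for time to discontinuation. No adjusted method is named for BMI or any other continuous outcome.

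Participants describes cohort 1 as prospective, with consent an inclusion criterion. Cohort 2 is retrospective and consecutive, "in reverse chronological order as registered in the CAUSA electronic health records", and consent is not an inclusion criterion. Both cohorts take patients "aged 12 to 35 years".

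**The concern.** A rank test with no covariates suits a randomised comparison better than this one. The article gives several reasons why the cohorts might differ at the start:

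- **Consent.** It selects patients into cohort 1 only. Effect and Sample Size allows for 25 of 75 eligible patients declining.
- **Start of follow-up.** Under Primary Outcome Measure, the clock starts in cohort 1 at the pharmacogenetics-informed prescription and in cohort 2 at the first antipsychotic prescription. Some cohort 1 patients may already have had an antipsychotic, so starting BMI could differ.
- **Growth.** Minors gain BMI as they grow. A different share of minors would produce a difference in BMI change that has nothing to do with care.

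At stake is the reading of one tolerability measure. Limitations relies on the other pragmatic outcome measures to control a tendency to keep a guided drug despite adverse events, so a spurious BMI difference could be misread as a sign of that tendency.

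**Working it through.** **The plan's own figure.** No figure is given for BMI. The stated 38 per cohort for the primary outcome reproduces with the arcsine effect size: h = 2·asin(√0.4) − 2·asin(√0.1) = 0.726; n = 2 × (2.80/0.726)² = 29.8, so 30; 30/0.8 = 37.5, so 38. Nothing below changes it.

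**Inputs.** From Effect and Sample Size: 50 per cohort, two-sided 0.05, and "an expected dropout or loss to follow-up rate of 0.2", which leaves 50 × 0.8 = 40. All BMI inputs are assumptions. The main set is: SD of one-year change 2 kg/m², baseline SD 3.5, extra growth in minors 0.4 to 0.8 per year, 30% minors in each cohort, true difference 1.0.

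**1. Balanced cohorts, 50 each.**
- BMI change: SE = 2 × √(2/50) = 0.40; 1.0/0.40 = 2.50; power = Φ(2.50 − 1.96) = 71%.
- Mann-Whitney on change, relative efficiency 0.955: 2.50 × √0.955 = 2.44; power 69%.
- Mann-Whitney on raw follow-up BMI: SD = √(3.5² + 2²) = 4.03; SE = 0.81; 1.0/0.81 = 1.24, times √0.955 = 1.21; power 23%.

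Simulation (4,000 trials per setting, with growth in minors included) gives 69% to 70% for regression, 67% to 68% for Mann-Whitney on change and 20% to 22% for Mann-Whitney on raw BMI. All comparisons of change and the regression reject a true null in about 5%.

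**2. Different age mix, 40% against 10% minors (illustration only).** Bias in mean change = growth × (0.40 − 0.10), which is 0.12 at 0.4 per year and 0.24 at 0.8 per year. At SE 0.40 the larger value is 0.6 standard errors, so null rejection is Φ(0.6 − 1.96) + Φ(−0.6 − 1.96) = 9.2%. Simulation gives bias 0.11 to 0.24 and rejection 5.2% to 9.0% for Mann-Whitney on change. For regression it gives bias about 0.01 and rejection 4.7% to 5.2%.

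**3. Different baseline BMI, 40 per cohort (second set of assumptions: SD 4, baseline to follow-up correlation 0.85).** With no true effect, a baseline gap D biases raw follow-up BMI by 0.85 × D and change by −0.15 × D. For D = 2 these are 1.70 and −0.30 kg/m². Simulated null rejection (1,500 trials per setting, with and without an age shift):

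| Baseline gap (kg/m²) | Mann-Whitney, raw BMI | Mann-Whitney, change | Regression |
|---|---|---|---|
| 0 | 4–5% | about 5% | about 5% |
| 1 | 11–14% | about 5% | about 5% |
| 2 | 35–44% | 6–9% | about 5% |

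**4. Cost of a missing baseline BMI.** If 30% of cohort 2 had none (assumed), 50 against 35 remain: SE = 2 × √(1/50 + 1/35) = 0.44; 1.0/0.44 = 2.27; power 62%, against 71% with all 100. A change score would lose the same patients.

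**The case against.** The strongest reply is that this is a condensed article, its list of tests is open, and an adjusted model may be in an analysis plan that is not shown. That stands in part. A reader might infer that no adjustment will be made; the text supports only that none is named. What remains is that the one method named fits the design poorly.

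The second reply is that a change score already does most of the work. That stands too: steps 1 and 3 show little gain over it unless the imbalance is marked. No part of the article shows that age mix or baseline BMI differs between the cohorts.

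A stronger reading is tempting. Participants admits patients "followed by clinical services for at least 1 year or earlier if there was evidence of antipsychotic treatment discontinuation", and Statistical Analysis says "patients will be followed up on for a year, from antipsychotic treatment initiation until discontinuation". A reader might infer that BMI is cut off at discontinuation, so that usual-care patients, who are expected to discontinue more often, have less time to gain weight. The article does not support this. The second sentence opens by limiting itself to the discontinuation analyses just described. Discontinuation concerns only the first drug and includes a cross-titration to another, after which a patient can still be in care and weighed. Medication changes are recorded over follow-up, and Economic Evaluation collects 12 months of service use in both cohorts. Short follow-up is possible for some patients, but nothing establishes it as a source of bias in BMI. A covariate for the timing of the BMI value would also be set by the primary outcome, which makes it a debatable adjustment.

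Finally, the unadjusted chi-square for the primary outcome shares the weakness and matters more. That is true, and it is why this point ranks low.

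**Conclusion.** The point holds as a modest improvement. The Mann-Whitney U cannot adjust for baseline BMI, age or sex in a comparison that is not randomised and includes minors, and one regression can. With balanced cohorts and BMI change as the outcome, the gain is close to nil. With the imbalances tried, the regression avoids a bias of up to 0.24 to 0.30 kg/m² and a false-positive rate of about 9% to 10%. It also avoids the large power loss that would follow if raw follow-up BMI were compared, though the article does not say that it would be. These sizes rest on assumed BMI inputs and illustrative imbalances. BMI is one unpowered part of a secondary outcome, so this is a change of lowest priority.

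**What to change.** In Statistical Analysis, state that BMI is compared using the value nearest 12 months after the start of follow-up as defined under Primary Outcome Measure. Use one linear regression of that value on cohort, baseline BMI (at the same start), age, sex and an under-18 indicator. Report the cohort coefficient with its 95% CI in place of the Mann-Whitney test, and report by cohort how many patients lack a baseline or follow-up BMI.

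The cost is a sentence or two of text and slightly more analysis; six parameters on 80 to 100 patients is feasible. There are two downsides. Patients without a recorded baseline BMI drop out of the model, most likely in cohort 2, and the article does not say how complete those records are. Calendar period, drug choice and the rest of the PRINT package stay unadjusted, so the coefficient should not be read as the effect of pharmacogenetic guidance alone.
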